## Abstract

**Introduction:**

Gliomas are the most common primary tumour of the central nervous system (CNS), with an estimated annual incidence of 6.6 per 100 000 individuals in the USA and around 14 deaths per day from brain tumours in the UK. The genomic and biological landscape of brain tumours has been increasingly defined and, since 2016, the WHO classification of tumours of the CNS incorporates molecular data, along with morphology, to define tumour subtypes more accurately. The Tessa Jowell BRAIN MATRIX Platform (TJBM) study aims to create a transformative clinical research infrastructure that leverages UK National Health Service resources to support research that is patient centric and attractive to both academic and commercial investors.

**Methods and analysis:**

The TJBM study is a programme of work with the principal purpose to improve the knowledge of glioma and treatment for patients with glioma. The programme includes a platform study and subsequent interventional clinical trials (as separate protocols). The platform study described here is the backbone data-repository of disease, treatment and outcome data from clinical, imaging and pathology data being collected in patients with glioma from secondary care hospitals. The primary outcome measure of the platform is time from biopsy to integrated histological–molecular diagnosis using whole-genome sequencing and epigenomic classification. Secondary outcome measures include those that are process centred, patient centred and framework based. Target recruitment for the study is 1000 patients with interim analyses at 100 and 500 patients.

**Ethics and dissemination:**

The study will be performed in accordance with the recommendations guiding physicians in biomedical research involving human subjects, adopted by the 18th World Medical Association General Assembly, Helsinki, Finland and stated in the respective participating countries’ laws governing human research, and Good Clinical Practice. The protocol was initially approved on 18 February 2020 by West Midlands – Edgbaston Research Ethics Committee; the current protocol (v3.0) was approved on 15 June 2022. Participants will be required to provide written informed consent. A meeting will be held after the end of the study to allow discussion of the main results among the collaborators prior to publication. The results of this study will be disseminated through national and international presentations and peer-reviewed publications. Manuscripts will be prepared by the Study Management Group and authorship will be determined by mutual agreement.

**Trial registration number:**

NCT04274283, 18-Feb-2020; ISRCTN14218060, 03-Feb-2020.

Strengths and limitations of this studyThe Tessa Jowell BRAIN MATRIX Platform (TJBM) study is a programme of work, which will improve the knowledge of glioma and treatment for patients with glioma.This platform study is a backbone data-repository of disease, treatment and outcome data from clinical, imaging and pathology data.The TJBM study will aim to provide rapid and accurate molecular diagnosis and a network of clinical hubs with robust protocols for the collection, processing, analysis and storage of tissue, images, and clinical and quality-of-life data.Gliomas occur at all ages and their specific subtype is difficult to predict preoperatively; therefore, the patient population eligible for the study is broad but currently excludes <16-year-old patients.

## Introduction

Gliomas are the most common primary tumour of the central nervous system (CNS), with an estimated annual incidence of 6.6 per 100 000 individuals in the USA,^1^ which is predicted to rise to 22/100 000 by 2035.^2^ In 2016, there were 5250 deaths from brain tumours in the UK, that is, 14 deaths per day.^2^ Malignant CNS tumours hold the poorest prognosis and are responsible for the highest estimated number of years of potential life lost (mean 20 years) among all cancers,^3^ and survival trends have remained generally static in comparison with other cancers.^4^

Gliomas have traditionally been divided into low-grade glioma (LGG; WHO I–II) and high-grade glioma (HGG; WHO III–IV) based on integrated classic histological features and molecular biomarkers.^5^ LGGs have an indolent course with patients commonly surviving a decade after diagnosis.^6^ However, the natural history of many WHO Grade II LGGs is progression to HGG. Approximately half of all newly diagnosed gliomas are classified as glioblastoma (GB; WHO IV), the most malignant type of brain cancer. Currently, the GB annual incidence is 3.2 per 100 000 population in the USA. This tumour occurs more frequently with advancing age; ranging from 0.4 per 100 000 population aged 20–34 years to over 15 per 100 000 population aged 75–84 years.^1^ It is widely recognised that elderly populations are rapidly increasing globally and this will have a significant impact on the burden of GB disease. Despite this, most studies still focus on patients younger than 65 years.

The current gold-standard treatment for newly diagnosed GB is surgical gross total resection, followed by radiotherapy with concomitant and adjuvant temozolomide. The aim of treatment is to delay tumour progression and extend overall survival.^7^ Despite decades of refinement, this approach results in a median survival time of only 12–14 months.

Over the last 20 years, the genomic and biological landscape of brain tumours has been increasingly defined, refining previous classification systems, unravelling intra-tumorous and inter-tumorous heterogeneity and progression, identifying drug targets and potential therapeutic strategies, and better characterising challenges to therapies, such as the blood–brain barrier and mutational escape. In 2016, WHO published its classification of tumours of the CNS,^5^ which for the first time used molecular data, along with morphology, to define tumour subtypes more accurately. This stratification integrated a combination of specific genetic and epigenetic biological characteristics that are changing rapidly as our knowledge evolves.^8^ In recognition of this rapid evolution of knowledge, ‘cIMPACT‐NOW’ (Consortium to Inform Molecular and Practical Approaches to CNS Tumor Taxonomy—Not Official WHO)^9^ was created, with the new WHO 2021^10^ classification representing a consensus opinion based on new insights into the molecular definition of brain tumours from this collaboration.^10^ As analytical technologies evolve and become more affordable, genome-wide analyses combined with other so-called ‘omics’ data will lead to further refinement of tumour classification with meaningful impacts on prognosis and choice of therapy. This is the motivation for the TJBM study, which will adopt whole-genome sequencing (WGS) and epigenomic analysis of tumour samples.

The TJBM study aims to create a transformative clinical research infrastructure that leverages National Health Service (NHS) resources to support research that is patient centric and attractive to both academic and commercial investors. Our approach will be holistic and flexible so that it can rapidly adapt to scientific advances and rigorously evaluate new drugs and technologies. To achieve this, it will establish a research-active network of clinicians and scientists who are well supported by an innovative trial infrastructure to deliver the following:

Rapid and accurate molecular diagnosis ensuring precise classification of tumours and identifying subsets of patients suitable for targeted therapy, by building on the legacy of the 100,000 Genomes Project.^11^
A network of clinical hubs resourced to maximise patient recruitment and collect tissue and data.Robust protocols for the collection, processing, analysis and storage of tissue, images and clinical and quality of life (QoL) data, building on existing infrastructure such as UK Biobank,^12^ Medical Research Council (MRC) Brain Banks Network^13^ and the CRUK PEACE study.^14^
High-quality biological samples that are fully clinically and radiologically annotated facilitating further biological and radiological research.Links to national and international clinical and scientific infrastructure and networks^15^; for example, Genomics England (GEL), European Network for Rare adult solid Cancer (EURACAN),^16^ SIOP-E Brain Tumour Group and National Cancer Research Institute Groups.Access to novel and repurposed drugs and technologies through collaborative partnerships with industry and early phase trials hubs and the structural genomics consortium (www.thesgc.org), to develop novel trials, within and outside, the TJBM infrastructure for testing of therapeutic strategies, including novel agents. As such, therapeutic clinical trials will be developed using this infrastructure to maximise efficiency in introducing and rigorously evaluating novel interventions. These will be separate protocols to the TJBM study.Long-term sustainability through delivery of clinically and scientifically meaningful outcomes, leveraged investigator-led research grants and an established cost-recovery model for biobanking.^17^

## Methods and analysis

### Study design

The TJBM study is a programme of work the principal purpose of which is to improve the knowledge of glioma and treatment for patients with glioma. The programme will include a platform study and subsequent interventional clinical trials (as separate protocols); figure 1. This platform study is the backbone data-repository of disease, treatment and outcome data from clinical, imaging and pathology data to be collected in patients with glioma from secondary care hospitals. Figure 2 shows an overview of the platform’s study schema.

**Figure 1 F1:**
[figure not shown]
Overview of the Tessa Jowell BRAIN MATRIX Programme. The Tessa Jowell BRAIN MATRIX Platform (TJBM) study will collect and integrate clinical, pathological, advanced molecular, imaging, quality of life, treatment and outcome data. The platform may provide data directly or support identification of eligible patients to clinical trials, within and outside the TJBM study programme. If eligible, patients may be enrolled in multiple add-on studies. Through consent and with strong governance processes, anonymised or pseudonymised data may be shared with other relevant organisations or studies within and outside the programme. GEL, Genomics England; NHS, National Health Service.

**Figure 2 F2:**
[figure not shown]
Study schema for the Tessa Jowell BRAIN MATRIX Platform study. GLH, Genomic Laboratory Hub; WGS, whole-genome sequencing.

The study aims to recruit 1000 patients within the UK over 5 years with participants followed up for up to 5 years. An initial 10 UK centres were opened to the TJBM study, as listed in online supplemental appendix 1, although further centre expansion is planned. The Standard Protocol Items: Recommendations for Intervention Trials (SPIRIT) checklist is provided as online supplemental appendix 2.^18^ The WHO Trial Registration Data Set is provided in online supplemental appendix 3.

10.1136/bmjopen-2022-067123.supp1Supplementary data

10.1136/bmjopen-2022-067123.supp2Supplementary data

10.1136/bmjopen-2022-067123.supp3Supplementary data

### Patient and public involvement

Patient and public involvement and engagement (PPIE) has been integral to this study from its inception. Our patient and public advisors, [name] and [name], co-developed the TJBM study by reviewing and refining the protocol and the participant-facing documents. They have provided input into the patient-reported outcome measures and have guided messaging about the study for the community. As members of the Study Management Group (SMG; online supplemental appendix 1), they continue to assess study conduct, and will contribute to the interpretation and dissemination of study findings through the PPIE dissemination strategy. This will include presentation of the study findings to identified audiences via the most appropriate channels, and to advise on messaging and their sensitivities.

### Patient selection

Patients aged ≥16 years with newly diagnosed suspected WHO Grade II–IV glioma (as evidenced radiologically) suitable for a diagnostic or therapeutic surgical procedure resulting in a tumour sample matched to a blood sample or with progression with known WHO Grade II–IV glioma will be eligible.

Patients with primary spinal cord tumours, who are receiving active treatment of other malignancy, have contraindications to MRI and/or without standard of care imaging available, will be excluded.

Newly diagnosed patients with suspected WHO Grade II–IV glioma who are subsequently found to have a WHO Grade I tumour or non-brain tumour are expected to be a rare occurrence. If this event occurs:

If it is confirmed as a Grade I tumour, then the patient will remain eligible for the study and will continue to be followed up in accordance with the protocol.If it is confirmed as a non-brain tumour, then the patient will not remain on the study and no further follow-up data will be collected.

All patients must be able to provide written informed consent for the study.

### Consent

Online supplemental appendix 4 contains exemplar informed consent forms, with online supplemental appendix 5 the patient information sheets (PISs) and lay summary for the study. The investigator or an appropriately trained delegate must obtain written informed consent for each patient prior to performing any study-related procedure. Remote consent for platform entry is permitted by telephone or video consultation instead of face-to-face consultations.

10.1136/bmjopen-2022-067123.supp4Supplementary data

10.1136/bmjopen-2022-067123.supp5Supplementary data

In addition to consenting to join TJBM, patients will be required to provide agreement for:

The collection and analysis of biological samples (eg, tumour, blood), including access to existing and future samples.The collection of relevant clinical information, including imaging and pathology.The return of clinically relevant results back to the referring clinician.The use of, and sharing of, data for research, teaching, commercial and scientific purposes, including data sharing through The Brain Tumour Charity’s BRIAN (the Brain tumouR Information and Analysis Network) database.^19^
The collection of different aspects of health data from the NHS and other Department of Health organisations (in addition to medical records) for longitudinal analysis and follow-up.The use of clinical data to identify potential clinical trials or other research that they may benefit from.The sharing of samples for other ethically approved research projects.

In addition, and in line with GEL processes and studies such as the 100,000 Genomes Project, optional consent will be taken as to whether the patient would like to receive feedback about the evidence of inherited diseases (both underlying the cause of the cancer and non-cancer causes).

For centres submitting tumour tissue for WGS through the standard of care (SoC) NHS Genomic Medicine Service (GMS) pathway in England, an additional GEL consent step is currently required to confirm consent at the point of referral for the patient’s clinical indication. This additional GEL consent step is performed electronically or on paper and can be completed over the phone.

### Platform assessments and schedule of events

Platform entry requires baseline clinical data, NIH Stroke Scale,^20^ weight and WHO Performance Status to be recorded, and then performed again at the start and end of concomitant therapy, the start and end of adjuvant therapy, further surgery and during the 5-year follow-up period.

In addition, QoL questionnaires will be completed at the initiation of concomitant therapy, initiation of adjuvant therapy, further surgery and during follow-up. The QoL booklet includes EQ-5D-5L,^21^ EORTC-QLQ-c30,^22^ Patient Concerns Inventory,^23^ Patient Global Impression of Change^24^ and Clinician Global Impression of Change.^25^

The schedule of events is included in online supplemental appendix 6.

10.1136/bmjopen-2022-067123.supp6Supplementary data

### Platform study outcome measures

The primary outcome measure of the platform is time from biopsy to integrated histological–molecular diagnosis (TTMD) defined as the difference (in days) between date of biopsy and date of WGS and epigenomic classification (EC).

Secondary outcome measures include those that are process centred, patient centred and framework based.

Process-centred secondaries include time to completion of each node of tissue and imaging pathway, tumour and biological sample(s) quality control (QC) status, imaging QC status and inter-rater agreement of response assessment in neuro-oncology (RANO).^26^

Patient-centred secondaries include extent of surgical resection, overall survival time (OS), intracranial progression-free survival time (PFS), QoL scores, type of interventions received, type of complications from treatments (standard of care) received, and concordance between initial local radiological diagnosis, local pathological diagnosis and integrated histological–molecular diagnosis.

Research framework–based secondaries include samples and images centrally stored, targetable mutation(s) identified, postmortem sampling consent status and sample collection confirmation, and number of applications to, and outputs resulting from, data repository (including trial proposals both within and outside of the TJBM network).

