### Statistical analysis plan

The target sample size for the study is 1000 patients. The primary remit of TJBM study is to establish a central data repository that will support the development and delivery of precision medicine for all patients with glioma in the UK. As such, there is no statistical basis behind the choice of target sample size, but this number will allow robust assessment of feasibility and subgroup analyses. Sample size for any clinical trials that are subsequently linked to the platform will be based on statistical justification.

A formal interim analysis of the primary outcome measure (TTMD) and any relevant secondaries will be performed after registration and diagnosis of the first 100 patients and after 500 patients. There are no formal stopping rules. Formal analyses of all study outcome measures will be performed once the study has completed recruitment (target 1000 patients) and completed the follow-up for all registered patients.

The analysis of TTMD will essentially be descriptive. The median TTMD will be reported overall and for each centre, together with the proportion of patients achieving TTMD within 28 days. Graphs of the change in both these summary statistics over time will be used to explore if TTMD changes during the course of the study. All estimates will be accompanied by 95% CIs. The time to completion of each node of tissue and imaging pathway will be reported as medians together with 95% CI, both overall and for each centre. Swimmer plots will be used to depict overall and node level timings for each patient.

For each type of tumour and biological sample, the proportion of sample passing QC and successfully undergoing WGS and EC will be reported with 95% CI and similarly for the imaging QC outcome measures. Inter-rater agreement of RANO will be assessed through Kendall’s coefficient of concordance.

Extent of surgical resection is evaluated from the postoperative MRI scan and is categorised as either closed biopsy, open biopsy, debulking <50%, subtotal resection 50%–90%, near total resection 90% to <100% or gross total resection 100%. The extent of surgical resection will be reported as the proportion falling into each category together with 95% CI.

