**Figure 3 F3:**
[figure not shown]
Sample and data flow pathways within the Tessa Jowell BRAIN MATRIX Platform (TJBM) study. *TJBM sites in England are encouraged to route all samples through their local NHS GMS GLH; however, if this pathway is not yet activated or GEL consent cannot be obtained, the TJBM Study Office can facilitate the processing of samples through an alternative NHS GMS GLH or via the GEL Research pathway. GEL, Genomics England; GLH, Genomic Laboratory Hub; GMS, Genomic Medicine Service; GTAB, Genomics Tumour Advisory Board; NHS, National Health Service; WGS, whole-genome sequencing.

Fresh tissue for TJBM must be frozen in liquid nitrogen and stored until shipment to the Oxford BRAIN MATRIX Laboratory. Matched ‘germline’ DNA from white blood cells is required for the detection of somatic variants for paired blood/tumour WGS. This should be collected as per standard GEL protocols. Ideally, it should be collected prior to or at the time of first surgery. The blood sample(s) must be shipped together with the frozen tissue of the patient to the Oxford BRAIN MATRIX Laboratory.

For patients who are not undergoing surgery and have available tumour samples from previous tumour surgery, blood should be collected and sent to the Oxford BRAIN MATRIX Laboratory along with their tumour samples.

For participants unable to donate a blood sample, a saliva sample is an acceptable alternative.

Where possible, it is intended to collect blood samples for liquid biopsies of the tumour (eg, tracking circulating tumour cell free (cft)DNA within the blood). Samples should ideally be collected at the time of operation, before the neurosurgeon performs any incision, ideally in theatres or the anaesthetics room just before any biopsy. Where feasible, further blood samples should be collected at the following key treatment milestones:

At first postoperative MRIInitiation of concomitant therapy (if applicable).The end of concomitant therapy (if applicable).Initiation of adjuvant therapy (if applicable).The end of adjuvant therapy (if applicable).The time of objectively measured progression.During the palliative phase if a post mortem has been agreed.

Where cerebrospinal fluid (CSF) is available for the patient, this should also be submitted.

Participating sites should follow the CRUK PEACE study protocol for postmortem neurological tissue donation. The aim of postmortem tissue donation is to enable research into:

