#### Sample analyses

Matched tumour/blood samples collected at first surgery are the most important samples of the TJBM study as these determine the initial integrated histological–molecular diagnosis. Following histological QC, the Oxford BRAIN MATRIX Laboratory will perform DNA extraction and QC; an aliquot will be sent to the Illumina Centre in Cambridge for WGS and one used for EPIC methylation array at the Wellcome Trust Centre for Human Genetics in Oxford. Remaining DNA and unused tissues will be stored at the BRAIN MATRIX Biorepository.

Raw WGS data will be maintained in the GEL Data Research Environment, where it can be accessed and re-analysed by data scientists at the submitting NHS Genomic Laboratory Hub or any qualifying TJBM-approved researcher. Sample data not generated by GEL will be consolidated in established bioinformatics hubs of the University of Oxford (Big Data Institute/Weatherall Institute for Molecular Medicine).

Data files on the Illumina 850k EPIC BeadChip analysis will be uploaded to the ‘Heidelberg Classifier’ hub at the German Cancer Centre in Heidelberg.^27^ This will generate an automated classifier report which will be stored at the Oxford BRAIN MATRIX Lab. Raw array data will be made available via the Oxford BRAIN MATRIX Laboratory.

Matched histological sections will be digitised at the Oxford BRAIN MATRIX Laboratory resulting in linked genomic data, which will initially be stored in Oxford. As the study evolves, we will aim to capture digital histological data from the material kept at the local neuropathology centre. The Oxford BRAIN MATRIX hub is working with CRUK-established data visualisation platforms, such as those developed for S:CORT (Colorectal Cancer)^28^ and based on international open access platforms (such as cBioPortal^29^).

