## Discussion

### Justification for patient population

The main aim of the TJBM study is to test the hypothesis that comprehensive genomic and epigenomic profiling of gliomas is feasible in a timely manner in the UK, and that the results improve stratification of patients for next-generation (targeted) therapies, ultimately improving outcomes and QoL.

Gliomas occur at all ages and their specific subtype is difficult to predict preoperatively. Therefore, the patient population eligible for the TJBM study is broad. It includes any patient who on preoperative assessment is suspected to have a diffuse glioma, or where a diffuse glioma remains a credible differential diagnosis, as established by the MDT at the recruiting site.

Recruitment is also open to patients with diffuse or atypical gliomas who had a biopsy before the launch of the TJBM study. This approach ensures that:

Patients with slow-growing diffuse gliomas that evolve over many years (oligodendrogliomas) may benefit from one or more of the clinical trials developed as part of the TJBM study and sample collection at tumour progression.Patients who potentially benefit most from comprehensive molecular diagnostics are not missed, which often are those with rare or atypical variants of glioma based on current diagnostics.^34^

The infrastructure for children with brain tumours in the UK is different to that of adults with epigenomic classification regularly used and with WGS shortly to be made available for all children with cancer. Thus, the challenges and opportunities are different for paediatric patients. Nevertheless, it is intended that children will be included within the TJBM study wherever appropriate. The recruitment of children and adolescents into the TJBM study will be coordinated with the UK’s paediatric oncology expert group(s).

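### TTMD is timed from biopsy, so patients diagnosed from archived tissue cannot meet the 28-day target; the primary summaries should be limited to biopsies taken at or shortly before registration

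*Protocol article*

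**What the plan says.** All references are to the protocol article.

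- **Outcome.** Under Platform study outcome measures, TTMD is "defined as the difference (in days) between date of biopsy and date of WGS and epigenomic classification (EC"). One definition serves all patients. It does not say which biopsy counts or how that biopsy relates to registration.
- **Summaries.** The Statistical analysis plan section reports the median overall and per centre, "together with the proportion of patients achieving TTMD within 28 days", and graphs both statistics over time. Formal interim analyses follow at 100 and 500 patients.
- **Eligibility.** Patient selection admits newly diagnosed patients having surgery, "or with progression with known WHO Grade II–IV glioma will be eligible". Justification for patient population adds: "Recruitment is also open to patients with diffuse or atypical gliomas who had a biopsy before the launch of the TJBM study". One stated reason is that "Patients with slow-growing diffuse gliomas that evolve over many years (oligodendrogliomas) may benefit" from later trials and from sampling at progression.
- **Tissue.** Under Biological samples, Sample collection: "For patients who are not undergoing surgery and have available tumour samples from previous tumour surgery, blood should be collected" and sent to the study laboratory with the stored tumour. Under Sample analyses, matched samples "collected at first surgery are the most important samples of the TJBM study as these determine the initial integrated histological–molecular diagnosis".
- **Exclusions.** Justification for methodology keeps brain tumours other than glioma out of the main analysis. The article states no exclusion or separate reporting for earlier biopsies, and the planned subgroups do not split new from archived tissue.

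**The concern.** The study's stated main aim includes showing that genomic and epigenomic profiling is feasible in a timely manner. TTMD is the only primary measure of that. For a patient diagnosed from archived tissue, much of the interval has passed before the platform could act, so the number reflects how long ago the operation was rather than how the pathway performs. Such a patient counts as a failure at 28 days by construction.

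This bias does not shrink with more patients. It also need not be equal everywhere. A centre that enrols more patients on stored tissue would look slower, and a changing share over calendar time would look like a change in the pathway.

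**Working it through.** The article gives no figure to reproduce: it says that the target of 1000 has no statistical basis, and it states no expected TTMD. The check is therefore on the definition and on the size of its effect.

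**Step 1: can an archived-tissue patient reach 28 days?**
Recruitment opened in November 2020 (Trial status). Take the latest possible opening day, 30 November 2020, and a patient biopsied before opening who registers on 15 June 2022, the approval date of protocol v3.0. If sequencing and classification follow registration, TTMD is at least the number of days between those dates, which is 562. More generally, any index biopsy more than 28 days before registration gives TTMD above 28 days.

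**Step 2: the 28-day proportion.**
Let p be the true proportion within 28 days among newly biopsied patients, and f the share of TTMD-evaluable patients analysed on archived tissue. These patients contribute nothing to the numerator, so the reported proportion is p(1 − f).

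| true p | f = 10% | f = 20% | f = 30% |
|---|---|---|---|
| 50% | 45% | 40% | 35% |
| 70% | 63% | 56% | 49% |
| 80% | 72% | 64% | 56% |

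For scale, the largest 95% CI half-width for a proportion is 1.96 × √(0.25/n): 3.1 points at n = 1000 and 9.8 points at n = 100. With p = 70%, the bias is 0.70 × f. It exceeds 3.1 points once f passes 0.031/0.70 = 4.4%.

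**Step 3: the median.**
If archived-tissue values all lie above the bulk of the others, the reported median is the 0.5/(1 − f) quantile of TTMD among newly biopsied patients. Assume, for illustration, a log-normal with median 28 days. The reported median is then 28 × exp(σ × z), where z is the normal quantile at 0.5/(1 − f).

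| f | quantile | σ = 0.5 | σ = 0.8 |
|---|---|---|---|
| 5% | 0.526 | 28.9 days | 29.5 days |
| 10% | 0.556 | 30.0 days | 31.3 days |
| 20% | 0.625 | 32.8 days | 36.1 days |
| 30% | 0.714 | 37.2 days | 44.0 days |

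The median is fairly stable at small f and moves appreciably only at larger shares.

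**Step 4: centres and trends.**
Take two centres with the same true 70%, one with f = 0 and one with f = 20%. They would report 70% and 56%, a gap of 14 points with no difference in performance. If 1000 patients were spread evenly over the initial 10 centres (an assumption), each would have about 100, and the gap would exceed the 9.8-point half-width. Likewise, if f fell from 30% to 10% during recruitment, the graph would rise from 49% to 63% with an unchanged pathway.

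**The case against.** **A journal article condenses a longer protocol.** Analysis sets and date rules are often left to that document, which may define a TTMD population. This limits the point to the published text but does not remove it. The article itself fixes the time origin, the eligibility and the 28-day summary, and these conflict for one admitted group. It does state a main-analysis exclusion for tumours other than glioma, and it uses registration as the origin for progression-free survival.

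**The share may be small.** TTMD exists only if sequencing and classification are completed. Justification for tissue collection calls fresh frozen material essential and paraffin collections not fully compatible with current genomic methods. Many old biopsies may therefore never yield a TTMD. This stands, and it is why f must be counted among TTMD-evaluable patients rather than among all patients with an earlier biopsy.

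**Patients entering at progression.** A reader might infer that none of them can reach 28 days. The documents do not support that: the article foresees sample collection at progression, and a patient timed from a new study biopsy is unaffected. The statement about first-surgery samples concerns the initial diagnosis and does not settle which biopsy starts the clock.

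**The analysis is descriptive.** There are no formal stopping rules, and no sample size rests on TTMD. Node-level medians and swimmer plots would make intervals of hundreds of days visible. That lowers the risk of misreading but leaves the headline proportion as it is.

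**Conclusion.** The definition and the eligibility conflict for patients diagnosed from archived tissue. For them TTMD includes time before registration, and the 28-day target is out of reach whatever the pathway does. The 28-day proportion is reduced by the factor (1 − f): with a true 70%, by 7 points at f = 10% and 14 points at f = 20%. That result assumes that these patients are in the denominator, that their tissue was taken more than 28 days before registration, and that sequencing and classification follow registration.

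It would be tempting to say that the overall and per-centre medians are worthless. The documents do not support this. Neither f nor the distribution of TTMD is given, and on the illustrative log-normal with log-SD 0.5 the overall median moves by about 2 days at f = 10%. Confounding of centre figures and trend graphs is conditional on f differing between centres or over time.

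This should be fixed. Because the outcome is descriptive and node-level timings are also planned, it does not threaten the study as a whole.

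**What to change.** 1. Define the index biopsy as the one that yielded the tissue sent for sequencing and classification. A patient with new surgery at progression is then timed from that surgery.
2. Restrict the primary TTMD summaries (overall median, per-centre medians, 28-day proportion, trend graphs) to patients whose index biopsy is at or after registration, or within a short stated window before it. The window should be well under 28 days, or the same difficulty returns.
3. Report archived-tissue patients separately, with the clock starting at registration or at laboratory receipt of the sample, and state how many there are.

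**Cost.** A short addition to the outcome definition and the analysis text. Biopsy dates are already needed for TTMD and registration dates for progression-free survival. The article does not list the date of sample receipt as a recorded item, so that should be confirmed before it is used as an origin. Slightly fewer patients enter the primary estimate: if all 1000 were evaluable and f were 10%, 900 would remain, and the largest half-width would go from 3.1 to 1.96 × √(0.25/900) = 3.3 points. The estimate would describe newly sampled patients only, which is the group in which pathway speed can be measured.
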